### Process evaluation

Successful nationwide implementation of the FeSS Protocols depends on the social and cultural context and behaviours of those delivering or receiving the intervention. Nurses and doctors acceptance and capacity to fully adhere to the Protocols is also central to maintaining intervention fidelity [67]. Hence, study outcomes (i.e. intervention success or failure) may be affected by factors related to the implementation or delivery of an intervention. Therefore, evaluation of the processes related to intervention delivery is important to provide insight into why interventions work or fail and how they can be improved.

A qualitative descriptive design will be used for the process evaluation. Frameworks for the design and reporting of the process evaluation of complex interventions developed by the United Kingdom Medical Research Council [68] and cluster randomised controlled trials [69] will inform the design, conduct and reporting of the process evaluation. At the conclusion of the trial, clinical champions, stroke unit/stroke service medical and nursing heads and bedside nurses implementing the FeSS Protocols will be approached by members of the research team requesting voluntary participation in semi-structured interviews and focus groups. Interviews and focus groups will examine the contributing organisational, contextual and structural factors that impacted successful/unsuccessful uptake of the intervention. Clinicians will be purposively sampled from high- and low-intensity external remote facilitation intervention hospitals further stratified by level of adherence (greater than or less than median; resulting in four strata) to the FeSS Protocols based on final trial results. We will sample a minimum of two hospitals from each stratum (*n*=8 hospitals) from which we will purposively sample one clinical champion, one medical head and one nursing head for interviews (*n*=3 interviews per hospital) and one focus group of bedside nurses from each hospital. Hence, we will undertake approximately 24 semi-structured interviews and eight focus groups, depending on saturation. Provision will be made for interviews and focus groups to be conducted virtually via videoconferencing or in person depending on the COVID-19 pandemic.

The focus group and interview questions will be designed using the Normalisation Process Theory [70]. The Normalisation Process Theory identifies and explains key mechanisms that promote and hinder the implementation, embedding and integration of complex interventions [70]. Two weeks prior to the focus groups and interviews, an information letter with details of the study including the procedure for consent will be provided to participants by the research team. Focus group and interview questions will be mainly open-ended and sessions will be conducted by an independent researcher member of the research team who has expertise in multi-method process evaluations of clinician practice change. Focus groups and interviews will be audio recorded, with the permission of participants, for ease of transcription. No identifiable information provided during interviews will be linked to individual participants with all identifiers removed before analysis. Voice recordings from the focus groups/interviews will be permanently deleted once a transcript of voice recordings is performed. All study materials will be disposed of in a confidential manner by shredding all focus groups/interviews transcripts and erasing all audiotapes and computer files.

### Outcome measures

The primary outcome is a binary measure of defect-free care. Defect-free care [71] is defined as adherence to a composite measure of six monitoring and treatment elements of the FeSS Protocols (Table 8). We have chosen one monitoring and one treatment element each from the Fever and Sugar Protocols and two elements from the Swallow Protocol, to be collected on the day of admission to the stroke unit/stroke service. These six elements were chosen as they are thought to be a proxy for better Protocol adherence for stroke care provided on day 2 and day 3 of hospital admission.

**Table 8 Tab8:** FeSS Protocol Outcome Measures

• ^b^*Fever Protocol* o **Temperature monitored at least four times per day on day of admission**^a^ o Temperature monitored at least four times per day on day 2 of admission o Temperature monitored at least four times per day on day 3 of admission o Paracetamol (or other antipyretic) given for first temperature ≥37.5°C o **Paracetamol (or other antipyretic) given with 1 h from first temperature ≥37.5°C**^a^ • ^b^*Hyperglycaemia (Sugar) Protocol* o Venous blood glucose level sample collected and sent to laboratory on admission to hospital o **Blood glucose levels (BGL) monitored at least four times per day on day of admission**^a^ o BGLs monitored at least four times per day on day 2 of admission o BGLs monitored at least four times per day on day 3 of admission (if BGLs unstable) o Insulin given for first BGL >10mmol/L o **Insulin given within 1 h from first BGL >10mmol/L**^a^ • ^b^*Swallow Protocol* o Formal swallow screen performed o Failed screen and subsequently had swallow assessment o Swallow screen performed within 4 h o **Swallow screen performed within 24 h**^a^ o Swallow assessment recorded o Swallow screen recorded o **Swallow screen or assessment performed before being given oral medications, food, or fluids**^a^	

^a^To be included in the primary composite outcome comprising six monitoring and treatment elements of the FeSS Protocols

^b^To be included in the secondary composite outcome of adherence to each of the combined monitoring and treatment elements for (i) fever, (ii) hyperglycaemia (sugar) and (iii) swallowing protocols

The secondary outcome measures are composite outcomes of adherence to each of the combined monitoring and treatment elements for (i) fever, (ii) hyperglycaemia (sugar) and (iii) swallowing protocols, and to the individual elements that make up each of these protocols (Table 8); comparison between metropolitan and rural/remote hospitals for composite outcome of adherence to each of the combined monitoring and treatment elements for (i) fever, (ii) hyperglycaemia (sugar) and (iii) swallowing protocols, and to the individual elements that make up each of these protocols; and comparison between stroke units and stroke services for composite outcome of adherence to each of the combined monitoring and treatment elements for (i) fever, (ii) hyperglycaemia (sugar) and (iii) swallowing protocols, and to the individual elements that make up each of these protocols.

The outcome for the economic evaluation will be the additional cost per quality-adjusted life year gained at 6 months post-stroke due to implementation of the FeSS Protocols. The process evaluation measure is the qualitative exploration of participants’ experience of contributing organisational, contextual and structural factors that impacted successful/unsuccessful uptake of the intervention.

### Sample size calculation

We used Monte Carlo simulation to estimate the detectable difference-in-difference between any two treatment arms with 80% power at a 5% significance level. Previous QASC Trial and QASC Europe studies suggest we could expect an ICC of 0.075, cluster level correlation between baseline and post-test of 0.3 and baseline defect-free care of 10%. With an assumed 60 hospitals with 60 patients included per hospital pre- and again 60 patients included post-intervention (i.e. *n*=120 patients per hospital and using an unequal randomisation ratio of 2 (high intensity):2 (low intensity):1 (no facilitation intensity), we calculated that a test between two 24 hospital arms would be able to detect a difference-in-difference of 1.5 (odds ratio (OR)) and a test between one 12 hospital arm and one 24 hospital arm would be able to detect a difference-in-difference of 2 (OR).

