Our team have recently completed the QASC Europe project, a collaboration between the Nursing Research Institute, the European Stroke Organisation, the European Registry of Stroke Care Quality (RES-Q) and the European Acute Networks Striving for Excellence in Stroke (Angels) Initiative—a not-for-profit organisation that aims to optimise the quality of treatment in all stroke centres. This study provided further evidence for successful external remote facilitation resulting in international uptake of the FeSS Protocols into 67 European hospitals in 17 countries [18–20]. The results showed statistically significant improvement pre-to-post-implementation in overall FeSS Protocol adherence (Pre 3.4%, Post 35%; Absolute difference 33%, 95% CI 24%, 42%; *p*<0.0001 )[17]. In this pre-test/post-test study conducted amid the COVID pandemic, we used an external facilitation model whereby hospital clinical champions, supported by the Angels Initiative, implemented the FeSS Protocols with ongoing email and telephone support co-ordinated remotely from Australia. Consequently, the intervention was able to be successfully delivered simultaneously to multiple international stakeholders across Europe. The various stakeholder groups played different roles involving a flow of information and change management from one stakeholder level to another. We called this a Cascading Facilitation model which involved interlocking partnerships and supported facilitation [21].

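### The detectable odds ratio of 1.5 for the primary high v low comparison does not follow from the stated inputs, and it does not pair with the odds ratio of 2 given for 12 v 24 hospitals

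*Protocol article*

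**What the plan says.** The Sample size calculation section describes its method as follows: "We used Monte Carlo simulation to estimate the detectable difference-in-difference between any two treatment arms", with "80% power at a 5% significance level". The assumptions are "ICC of 0.075, cluster level correlation between baseline and post-test of 0.3 and baseline defect-free care of 10" per cent, in 60 hospitals with 60 patients before and 60 after implementation, allocated 2:2:1. This gives arms of 24, 24 and 12 hospitals.

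Two results follow from this one set of inputs. For the two active arms, "a test between two 24 hospital arms would be able to detect a difference-in-difference of 1.5 (odds ratio (OR". For an active arm against control, "a test between one 12 hospital arm and one 24 hospital arm would be able to detect a difference-in-difference of 2 (OR".

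Under Study aims, high v low intensity is the primary comparison, so the 1.5 is the figure that supports it. The Data analysis section specifies patient-level logistic regression allowing for correlation within hospitals. It does not say how the baseline period enters the model.

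**The concern.** Two things look wrong. First, halving one arm from 24 to 12 hospitals raises the standard error by a known factor, and the step from 1.5 to 2 is much larger than that. Second, a pre-post hospital correlation of only 0.3 means that hospitals vary a good deal between periods for reasons unrelated to allocation. With 24 hospitals per arm, that variation alone makes an odds ratio of 1.5 hard to detect.

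The Discussion defends the unequal allocation on the ground that it lets the trial detect smaller differences between the active arms. If power at 1.5 is well below 80%, a non-significant high v low result could be read as showing that the cheaper strategy does as well, when the design had only a modest chance of seeing a difference of that size. The planned business case would build on that reading.

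**Working it through.** **Inputs.** From the Sample size calculation section: ICC 0.075, pre-post cluster correlation 0.3, baseline 10%, 60 + 60 patients per hospital, arms of 24, 24 and 12, 80% power, 5% level. Assumed because not stated there: a two-sided test, the ICC scale (both tried), and the comparator's post-implementation rate (10% to 50%).

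**1. Do the two stated effects fit together?** With equal per-hospital variance, the detectable log odds ratio is proportional to √(1/n₁ + 1/n₂).
- Expected growth: √((1/12 + 1/24)/(2/24)) = 1.22.
- Stated growth: ln 2 / ln 1.5 = 0.693/0.405 = 1.71.
- If 1.5 is right, 12 v 24 detects 1.5^1.22 = 1.64. If 2 is right, 24 v 24 detects exp(0.693/1.22) = 1.76, and power at 1.5 is about 52%.
- Rounding does not explain it: 1.549 maps only to 1.71.

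Different post rates in the two comparisons could widen the factor, but no two-sided combination tried brought the first figure down to 1.5.

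**2. Between-hospital variance.** Latent scale: 0.075/0.925 × π²/3 = 0.267 on the logit scale.

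**3. Literal difference-in-difference, 24 v 24, odds ratio 1.5.** Per-hospital variance = 2 × 0.267 × (1 − 0.3) + 1/(60 × 0.1 × 0.9) + 1/(60 × p(1 − p)), where p is the post rate.
- Comparator at p = 10%: 0.373 + 0.185 + 0.185 = 0.744. Other arm at p = 14.3%: 0.373 + 0.185 + 0.136 = 0.695 (sums taken before rounding).
- SE = √((0.744 + 0.695)/24) = 0.245. Power = Φ(0.405/0.245 − 1.960) = 38%.
- At higher post rates, power rises to 43%.
- Solving ln OR = (1.960 + 0.842) × SE gives a detectable odds ratio of 1.97 at a 10% post rate and 1.90 at 35%.

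**4. Adjusting for hospital baseline.** Per-hospital variance = post variance − covariance²/pre variance, with covariance 0.3 × 0.267 = 0.080 and pre variance 0.267 + 0.185 = 0.452. The reduction is 0.080²/0.452 = 0.014.
- At a 10% post rate: 0.438 and 0.389, SE = 0.186, power 59%, detectable odds ratio 1.68.
- At 35%: 0.326 and 0.320, SE = 0.164, power 70%, detectable odds ratio 1.58.

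**5. Unlimited patients per hospital.** A difference-in-difference detects exp(2.802 × √(2 × 0.373/24)) = 1.64. With baseline adjustment the variance is 0.267 × (1 − 0.09) = 0.243 and the limit is 1.49. So 1.5 is roughly the best attainable with infinite audits, not the result for 60.

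**6. ICC on the proportion scale.** The logit variance is 0.075/(p(1 − p)) at each rate, for example 0.833 at 10% and 0.330 at 35%. The same formulas give power at 1.5 of about 21-27% for a difference-in-difference and about 34-66% with baseline adjustment.

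**7. 12 v 24 at odds ratio 2, latent scale, control the smaller arm.** Difference-in-difference at a 10% post rate: SE = √(0.744/12 + 0.671/24) = 0.300, power = Φ(0.693/0.300 − 1.960) = 64%, rising to 70% at higher rates. With baseline adjustment, power is 86-93%.

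**8. Simulation (latent scale, post rates 10-35%).** 3,000 runs for hospital-level tests, 400 for mixed models.

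| Analysis | 24 v 24, OR 1.5 | 12 v 24, OR 2 |
|---|---|---|
| t test on change in logits | 33-39% | 58-63% |
| t test on change in proportions | 39-64% | 67-89% |
| Mixed model, difference-in-difference | 38-42% | 64-68% |
| Hospital-level baseline adjustment | 52-66% | 80-91% |
| Mixed model, common baseline | 60-69% | 87-94% |

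A mixed model with a random hospital intercept only reached 64-70% at 1.5, with a type I error of about 16%.

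**The case against.** The strongest defence is that an article condenses its methods. It gives neither the ICC scale, nor sidedness, nor the simulated model, so no single power figure can be pinned on the authors. That stands, and it is why the result is given as a range. It does not rescue the 1.5, because no two-sided reading tried reaches 80%.

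Stronger conclusions that a reader might infer are not supported:
- **Power is simply 35-40%.** That is one reading: a change-from-baseline analysis with a latent-scale ICC. The phrase difference-in-difference favours it, but the Data analysis section does not settle the point.
- **The odds ratio of 2 is also wrong.** Baseline adjustment reaches it. Only the literal difference-in-difference falls short.
- **The two figures flatly contradict each other.** If 1.5 were right, 2 would merely be conservative. They are inconsistent only as two 80%-power thresholds from one calculation.
- **The 1.5 must come from ignoring hospital-by-period variance.** Other departures also approach it. A one-sided 5% test with baseline adjustment gives 1.50-1.58, and treating 0.075 as the logit variance with baseline adjustment gives 83% power. Where these get to 1.5, 12 v 24 has 95% power or more at an odds ratio of 2, so the pair still does not match.
- **The 10% baseline conflicts with the Background figures ("Pre 3.4%, Post 35%; Absolute difference 33" per cent).** Those describe overall adherence in European hospitals. Nothing shown says that they measure this trial's six-element, day-of-admission composite, and the inputs are said to draw on two earlier studies.

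**Conclusion.** The point holds for the 24 v 24 figure. On the stated ICC, correlation, cluster size and baseline, a two-sided 5% test does not give 80% power at an odds ratio of 1.5. With a latent-scale ICC the shortfall is to about 38-43% (difference-in-difference on the log-odds scale) or about 50-70% (baseline-adjusted), and it is generally larger with a proportion-scale ICC. The matching detectable odds ratios on the latent scale are about 1.9-2.0 and about 1.6-1.7.

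The 1.5 and the 2 are also inconsistent as a pair from one calculation. The error is located in the 1.5; the 2 remains attainable with baseline adjustment.

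Confidence is high that 1.5 does not follow from the inputs and moderate for any single power value, since the ICC scale, post rates and model are assumptions here.

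**What to change.** Rerun the simulation with the model planned for the primary analysis, including hospital variation between periods at the stated correlation of 0.3. Then restate the 24 v 24 detectable odds ratio. On present inputs and a latent-scale ICC, expect about 1.9-2.0 for a difference-in-difference, or about 1.6-1.7 if the primary analysis adjusts for the hospital baseline rate. Take the 12 v 24 figure from the same run. A sentence giving the ICC scale, sidedness, assumed post-implementation rates and handling of baseline would let readers check the result.

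If the choice of model is still open, adjusting for baseline recovers much of the lost power. The cost is a rerun and a less favourable published figure; no hospitals or patients need be added.

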### Data analysis

#### Primary and secondary outcomes

The unit of analysis is at the patient level. Analysis will be by intention-to-treat. Demographic and clinical characteristics of patients (e.g. treatment in a stroke unit, discharge destination, ability to walk on discharge, duration of hospital stay, discharge modified Rankin Scale score) will be summarised using descriptive statistics and presented by group allocation. Analysis for overall adherence with all monitoring and treatment elements of the FeSS Protocols and adherence to each of the monitoring and treatment elements for Fever, Sugar and Swallowing will be undertaken based on the following comparisons: low-intensity facilitation versus control groups, high-intensity facilitation versus control groups and low-intensity facilitation versus high-intensity facilitation groups. Analysis will include comparison of outcomes between metropolitan and rural/remote hospitals; difference in proportions of change in monitoring and treatment for fever, hyperglycaemia and swallowing between stroke units versus stroke services. Analysis of outcomes will use logistic regression with adjustment for rurality, stroke unit presence; presence of Angels consultants; baseline thrombolysis rate (<11% vs ≥11%; 11% is the average annual rate based on the 2021 Stroke Foundation clinical audit) [5]; age, sex, stroke severity and correlation of outcomes within hospitals. Effect sizes will be estimated for each intervention group relative to the control as well as for comparisons between the low-intensity facilitation and high-intensity facilitation intervention groups. No interim analyses are planned.

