In 2017, a ‘strong recommendation’ for use of standardised protocols to manage fever, glucose and swallowing difficulties in patients following acute stroke was included in the Australian and New Zealand Clinical Guidelines for Stroke Management [4]. However, the most recent 2021 Australian national acute services stroke audit showed that fever, hyperglycaemia and swallow management remained sub-optimal with only half (50%) of patients with fever ≥37.5°C receiving paracetamol within an hour, only 29% receiving insulin within 1 h of the first elevated finger prick glucose ≥10mmol/L and only 60% of patients receiving a swallow screen/assessment prior to oral medications, food, or drink [5]. In New Zealand, the most recent nationwide stroke audit in 2018 was conducted as part of the Reducing Ethnic and Geographic Inequities to Optimise New Zealand Stroke Care (REGIONS Care) Study. The findings showed that only 34.7% of ischemic stroke patients in urban hospitals and 32.5% of those in non-urban hospitals received a swallow assessment within 6 h of hospital arrival, with no significant difference between both groups (adjusted odds ratio 0.94, 95% confidence interval 0.74–1.18) [6]. Management of the other two FeSS Protocol elements (fever and hyperglycaemia) were not included in the audit hence it remains unclear whether or not these physiological parameters are being monitored and treated appropriately in New Zealand. The Australian and New Zealand audit results highlight that a significant evidence-practice gap remains in translation of the FeSS Protocols into standard stroke care across these countries. Achieving knowledge translation and sustaining adherence to evidence-based interventions is often difficult [7]. There is a need for systematic support to further improve adherence to the FeSS Protocols.

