### Study setting

Australian and New Zealand public and private hospitals with a stroke unit or stroke service.

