Participating hospitals will also be asked to complete a short online organisational survey to obtain information about structural workplace characteristics and resources available to deliver acute stroke care to allow for more accurate data comparison. Data to be collected include presence of stroke unit, bed capacity, availability of multidisciplinary and specialist staff, annual thrombolysis rate (previous 12 months) and presence of stroke care facilitators from the Angels Initiative (a not-for-profit organisation that aims to optimise the quality of treatment in stroke centres [https://www.angels-initiative.com/]).

All data will be stored, managed and archived in accordance with National Health and Medical Research Council requirements. Electronic data will be stored on password-protected networked drives linked to the Nursing Research Institute and accessible only by the researchers. The final trial data set will be archived in a data repository. Only de-identified data will be analysed. The study findings will be communicated via publication in peer-reviewed scientific journals.

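### The outcome model splits each hospital's thrombolysis rate at 11% although the rate itself is collected; this costs a little precision and causes no bias

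*Protocol article*

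**What the plan says.** Under Data analysis, Primary and secondary outcomes, the protocol article specifies logistic regression with a list of hospital and patient adjusters. One of them is "baseline thrombolysis rate (<11% vs ≥11%; 11% is the average annual rate" in a 2021 audit. The reference cited there is the one behind the Background's statement of what "the most recent 2021 Australian national acute services stroke audit showed", so the cut is an Australian figure. Study setting covers "Australian and New Zealand public and private hospitals with a stroke unit or stroke service", and no separate New Zealand value is given. The only reason offered for 11% is that it is the audit average.

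The rate itself will be available. Under Data collection, "Participating hospitals will also be asked to complete a short online organisational survey", and one of its items is "annual thrombolysis rate (previous 12 months"). Study procedure and Table 5 place this survey before the pre-implementation audit, and so before randomisation.

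The Sample size calculation works in terms of a difference-in-difference "with 80% power at a 5% significance level". It assumes "an ICC of 0.075, cluster level correlation between baseline and post-test of 0.3 and baseline defect-free care of 10" per cent, with 60 patients per hospital in each period and arms of 24, 24 and 12 hospitals. The analysis section does not say whether the regression is a difference-in-difference, a baseline-adjusted or a post-only model.

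**The concern.** As a two-level factor, the covariate treats a hospital that never thrombolyses like one at 10%, and puts hospitals at 10.9% and 11.1% in opposite groups. An average need not be the median, and the trial admits regional and rural sites and services without a dedicated stroke unit, so the hospitals could divide unevenly at 11%.

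With 24, 24 and 12 hospitals, between-hospital variation is a large part of the uncertainty in every comparison. Whatever the rate could explain and the split does not capture stays as residual variance and as unadjusted chance imbalance. The question is how much that amounts to.

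**Working it through.** **Inputs from the protocol article (Sample size calculation).** ICC 0.075; pre-post hospital correlation 0.3; baseline adherence 10%; 60 patients per hospital per period; 24 versus 24 hospitals; 80% power; 5% significance, taken as two-sided.

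**Assumptions.** The share of hospital variance explained by the rate (R², or r² for a correlation r) is not in the documents; the range 0.10 to 0.30 is used. The ICC is read on the latent logit scale.

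**The plan's own figures.** The stated detectable odds ratios are 1.5 (24 versus 24) and 2 (12 versus 24). Cluster-level approximations gave 1.59 to 2.73 and 1.76 to 3.41, depending on the scale of the ICC, the post rate and the estimator. The 1.5 was not reproduced. The simulation model behind these figures is not described, so this says nothing either way about the present point. What matters below is the difference between two forms of one covariate.

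**Step 1: share of explained variance kept.** For a normal covariate with a linear effect, cut at quantile q, the share kept is φ(z_q)² / [q(1 − q)].

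| Split | Share kept |
|---|---|
| 50/50 | 64% (= 2/π) |
| 30/70 | 58% |
| 20/80 | 49% |
| 10/90 | 34% |

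**Step 2: variance components.**
- Hospital variance s = (0.075/0.925) × π²/3 = 0.267.
- Sampling variance before: e0 = 1/(60 × 0.10 × 0.90) = 0.185.
- Sampling variance after, at 14.3% (an odds ratio of 1.5 on 10%): e1 = 1/(60 × 0.143 × 0.857) = 0.136.

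Let k be R² times the share kept (the whole of R² for a continuous term). Then V_post = s(1 − k) + e1, V_pre = s(1 − k) + e0, and the pre-post covariance is C = s(0.3 − k).

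**Step 3: difference-in-difference.** The variance is V_post + V_pre − 2C = 2s(1 − 0.3) + e0 + e1 = 0.695. The k cancels. The detectable odds ratio is exp[2.80 × √(0.695 × 2/24)] = 1.96 with either form, at any R².

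**Step 4: baseline-adjusted analysis.** The variance is v = V_post − C²/V_pre, and the detectable odds ratio is exp[2.80 × √(v × 2/24)].

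| R² | Median split | Continuous | Difference |
|---|---|---|---|
| 0.10 | 1.643 | 1.635 | 0.008 |
| 0.20 | 1.629 | 1.611 | 0.018 |
| 0.30 | 1.613 | 1.583 | 0.030 |

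A 20/80 split gives 1.646 and 1.624 at R² 0.10 and 0.30, so the differences become 0.011 and 0.041. Simulated power at an odds ratio of 1.5 (6,000 runs) rises from 53% to 55% at R² 0.10 and from 57% to 60% at R² 0.30. Each figure has a Monte Carlo error of about √(0.55 × 0.45/6000) = 0.6 points.

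If the ICC is read on the proportion scale, s = 0.075/(0.10 × 0.90) = 0.833. The median-split to continuous changes are then 2.132 to 2.114 and 2.062 to 1.986, on a much larger detectable effect.

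**Step 5: post-only analysis.** Assume a post rate of 25%, so e1 = 1/(60 × 0.25 × 0.75) = 0.089. The ratio of continuous to median-split variance is [s(1 − r²) + 0.089] / [s(1 − 0.637r²) + 0.089]. At r = 0.3 it is 0.974, a 2.6% reduction, worth 48 × (1/0.974 − 1) = 1.3 hospitals. At r = 0.5 it is 0.923, a 7.7% reduction, worth 4.0 hospitals.

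**Step 6: how large r can be.** A stable hospital trait that correlates r with adherence in both periods by itself induces a pre-post correlation of r². Unless other influences are negatively correlated over time, r² cannot exceed 0.3, so r is at most √0.3 = 0.55. At r = 0.5 the rate alone would account for 0.25/0.3 = 83% of all stable between-hospital variation. If 0.3 refers to observed proportions, the correction for sampling noise is 0.3/√[(0.267/0.452) × (0.267/0.356)] = 0.45, so r is at most 0.67.

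**The case against.** The best defence is that the cut is external and fixed in advance, so nobody can choose a favourable split. The documents say nothing about the shape of the relation, and if it were a threshold a straight line need not do better. The model already adjusts for rurality, stroke unit presence and Angels consultants, and randomisation is stratified by country, registry participation and remoteness. Only the association that remains after those factors counts, which pushes R² towards the low end. If the primary contrast is the difference-in-difference used for the sample size, and the Discussion also speaks of comparing pre-post changes, a time-constant hospital covariate drops out and nothing is gained.

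Most of this stands, and it limits the size of the point. It does not justify the cut. A linear term can be fixed in advance just as easily, and in a difference-in-difference the two-level factor adds nothing to the treatment contrast either.

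A reader might infer that 11% is wrong for New Zealand. The documents give no New Zealand thrombolysis rate, so an off-centre split there is only a possibility.

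**Conclusion.** The point holds as a minor one. The protocol fixes a coarse form for a covariate that it collects in full, and gives no modelling reason. If the rate is roughly normal and acts linearly, the split keeps at most about 64% of what the rate could explain.

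The price is small: 0.01 to 0.03 on the detectable odds ratio, or 1 to 3 points of power, with baseline adjustment, a median split, the ICC on the latent scale and an assumed R² of 0.10 to 0.30. It is about 2.6% of contrast variance in a post-only analysis at an assumed r of 0.3, and essentially nil in a pure difference-in-difference.

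Two stronger readings are not supported:
- A reader might infer a loss worth many hospitals, since r = 0.7 in the post-only formula gives 17%, or about 10 hospitals in 48. That value conflicts with the protocol's own pre-post correlation of 0.3, on either reading of it. Even r = 0.5 should be taken as an upper bound.
- A reader might infer a biased treatment effect. Hospitals are randomised, so the cut affects precision and adjustment for chance imbalance only.

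**What to change.** Pre-specify the annual thrombolysis rate as a single continuous linear term in the outcome model, before outcome data are analysed, and keep the 11% split for descriptive tables only. This changes one line of the model specification, needs no new data and uses the same one degree of freedom as the two-level factor. An indicator for hospitals that do not thrombolyse, or a low-order spline, is optional. Either would use extra hospital-level degrees of freedom, which are scarce with 60 hospitals.
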